#### 8.9.6. Final analysis of hospice care

Analysis of admission to hospice care will be performed using Bayesian Logistic regression with uninformative priors. The endpoint will be defined as any admission to hospice by day 90 post-discharge; any hospice care will be considered a successful outcome, while death within 90 days or survival without hospice care will be considered as non-successful outcome. The linear predictors the model will mimic that of the primary analysis in 8.3.3. From this model, we will estimate the following quantities:

- Posterior probability of superiority of each active arm over STS in terms larger odds of admission to hospice within 90 days.
- Posterior probability of superiority of each active arm over all other active arms in terms larger odds of admission to hospice within 90 days.

#### 8.9.7. Sensitivity analyses exploring the potential impact of payer type

On August 10, 2022 the trial expanded its inclusion criteria to include Medicare Fee-For-Service (MC FFS) patients. We will conduct two types of sensitivity analyses to detect any differences in PDHD distribution between UPMC Health Plan and MC FFS patients:

- We will fit two additional proportional logit models accounting for payer type:
  - One logit model including a term for payer which will capture proportional shifts in home days across payer groups; and
  - A second model that will include different intercept terms for the payer type groups. This model will capture non-proportional shifts in home days across both groups.

- We will explore potential differential effects of RPM care models across payer types. One model will estimate interaction terms between RPM arm and payer type; and another will fit separate proportional logit models to UPMC Health Plan and MC FFS participants. We will also explore limiting these analyses to data collected after August 10, 2022 when MC FFS patients were eligible.

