## Data Collection

Quantitative data is collected from several sources. Self-report assessments are gathered at baseline and 90-days using REDCap Cloud, a secure data collection platform. Clinical data, additional patient demographic/descriptive information, and health care utilization data is extracted from electronic health records and payer claims at baseline and 90-days. For individuals who withdraw from the study, data will be retained up to the point of study withdrawal.

Qualitative telephone interviews are conducted to understand patient or caregiver intervention-related experiences. We will conduct interviews with 80 patients (spread approximately evenly across each of the 4 intervention arms). If a patient is unable to participate in an interview due to medical complexity, we attempt to interview his/her primary caregiver. All audio recordings of interviews are transcribed by experienced qualitative researchers and de-identified. We use a unique study ID to label all study materials related to participation with a tracking log as the only link to identifying information. Transcripts will be stored on a secure cloud-based environment approved by UPMC.

We use the NVivo 12 (QSR International, Australia) platform for data analysis. A constant comparative thematic content approach will be used to analyze the qualitative data. Our qualitative analysis is iterative. A separate codebook is developed for each interview type (i.e. patient, intervention providers, primary care physicians) with the input of the Co-Investigators and the Stakeholder Advisory Board. We assess inter-rater reliability using percent agreement and kappa scores. Upon acceptable interrater reliability, the qualitative research team thematically codes all qualitative documents.

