## 6. ENDPOINTS

### 6.1. Primary endpoint

The primary efficacy endpoint will be post-discharge home-days (PDHD) recorded over the first 90 days after discharge to the patient's home. Patients will be assigned -1 days if they die before day 90 post-discharge home. Among patients who survive 90 days or more, PDHD is recorded as the total number of days alive and out of acute care hospitals or post-acute care facilities (e.g., inpatient rehabilitation, skilled nursing facilities, long-term care facility). If a patient is readmitted to one of these facilities during the 90 days after returning home, then those days not at home will be subtracted from their PDHD. The following rules will be used to calculate PDHD.

- Home is defined as any location that does not involve insurance claims charged to UPMC Health Plan. This can include the patient's own residence, someone else's residence (family or friend), independent living facility or personal care home. It is not restricted to being the same location at which the patient resided pre-admission, so long as it does not involve UPMC Health Plan claims.
- The index hospitalization and post-acute health care facilities (e.g., long-term acute care facility, ventilator-rehabilitation unit, rehabilitation facility, transitional care units, skilled nursing care, nursing homes) visited following discharge are counted as "hospitals" until the patient is discharged home.
- PDHD can take on integer values from -1 to 90. Any calendar day partially spent in acute care hospitals or post-acute care facilities is counted as a full day for the purposes of calculating PDHD, regardless of whether it was part of the initial admission or any readmission.

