#### 8.9.8. Sensitivity analysis limited to UPMC Health Plan members with coverage for the duration of follow up

We will conduct an analysis limited to patients with UPMC Health Plan coverage throughout the duration of the 90-day follow up period. FFS patients, as well as UPMC Health Plan members who lose or drop their coverage under the Plan before the end of the 90-day follow up period, will be excluded from this analysis. Outcomes ascertainment could be more accurate among patients included in this analysis. This analysis will be conducted using the model in 8.3.3.

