## 8.11. *Handling of missing data*

### 8.11.1. *Missing PDHD data*

The primary endpoint is ascertained using claims data for the majority of patients, and medical records review for the small subset of patients that either drop UPMC Health Plan coverage during the course of follow up, or are covered by the Medicare Fee-for-Service program. We will assume that no record of death or readmissions counted against the primary endpoint correctly correspond to the absence of these events for the patient, and therefore the primary outcome will be completely observed for all patients.

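### The payer-term and payer-intercept models in Section 8.9.7 compare home days taken mainly from claims with home days taken from records review, so a payer difference may be only a data-source difference

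*Combined protocol and SAP*

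**What the plan says.** Appendix Section 8.9.7 adds payer analyses after fee-for-service patients became eligible on August 10, 2022. Their stated aim is "to detect any differences in PDHD distribution between UPMC Health Plan and MC FFS patients". There are four models: a payer term, payer-specific intercepts, arm-by-payer interactions, and separate fits by payer. The section also offers to explore restricting the data to the period after that date. The protocol (Measures, Covariates, Payer) repeats the models and has home-days distributions by payer reported quarterly to the DSMB.

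Section 8.11.1 fixes the source of the endpoint: "The primary endpoint is ascertained using claims data for the majority of patients, and medical records review for the small subset of patients" who "either drop UPMC Health Plan coverage during the course of follow up, or are covered by the Medicare Fee-for-Service program". It then assumes that "no record of death or readmissions counted against the primary endpoint correctly correspond to the absence of these events".

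Section 8.9.8 limits one analysis to continuously covered Health Plan members, on the ground that "Outcomes ascertainment could be more accurate among patients included in this analysis".

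Two other places bear on the source. Section 6.1 says "Home is defined as any location that does not involve insurance claims charged to UPMC Health Plan". The protocol's summary table of measures lists claims, EHR, health information exchange (HIE) and participant report for home days, with no split by payer.

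**The concern.** Apart from members who lose coverage, Section 8.11.1 lets payer decide how the endpoint is found. The error also has a direction. A facility stay that records review does not find becomes home days, and a death that it does not find becomes survival. Both raise home days in the fee-for-service group.

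None of the 8.9.7 models mentions source. Restricting to the period after August 10, 2022, like the three-month time terms in Section 8.3.2, aligns calendar time but leaves the two sources as they were. Section 8.9.8 recognises the ascertainment question, but it drops the fee-for-service patients and so cannot separate payer from source.

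What is at stake is the reading of the payer shift. An apparent advantage for fee-for-service patients could be a measurement artefact. An apparent absence of difference could be a real deficit cancelled by missed events. The plan has no step that would show which.

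**Working it through.** **Inputs.** Table 2 (Section 12.2), baseline population: death 0.133; 0-19 0.005; 20-39 0.017; 40-49 0.017; 50-59 0.026; 60-69 0.042; 70-79 0.077; 80-89 0.228; 90 days 0.454. These sum to 0.999 and were rescaled to 1. Survivors with fewer than 90 days make up 0.412. Stratum odds ratios are 0.75 (severe) and 0.35 (SNF), from Section 12.1. Total enrolment is 1,281 (protocol synopsis). The documents give neither a miss rate nor the number of fee-for-service patients; both are assumed over a range.

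**Reproducing the plan.** Shifting Table 2 by logit P(Y ≤ j) − log(OR) reproduces all 24 probabilities in Table 4 to within 0.01. For OR 1.00: severe 0.170 (death) and 0.385 (90 days) against 0.17 and 0.38; SNF 0.305 and 0.226 against 0.31 and 0.23. For OR 1.50, baseline: 0.093 and 0.555 against 0.09 and 0.55.

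**Payer shift from source alone.** Give both payers the Table 2 distribution. In fee-for-service, move a share m of survivors with facility days to 90, as the 8.11.1 rule would do if none of their stays were found. In a second version, move the same share of deaths to 90 as well. The payer odds ratio is the large-sample proportional-odds fit of observed fee-for-service against Health Plan, with equal weights.

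Example, m = 20%, deaths all found: P(90) = 0.454 + 0.20 × 0.412 = 0.536 (0.537 after rescaling). The odds ratio at the 90-day cut is (0.537/0.463)/(0.454/0.546) = 1.39. At the death cut it is 1.00. The common odds ratio over all cuts is 1.28.

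| Share missed | P(90), stays missed | Payer OR, stays missed | Payer OR, deaths missed too |
|---|---|---|---|
| 0% | 0.454 | 1.00 | 1.00 |
| 5% | 0.475 | 1.06 | 1.10 |
| 10% | 0.496 | 1.13 | 1.21 |
| 20% | 0.537 | 1.28 | 1.47 |
| 30% | 0.578 | 1.46 | 1.81 |

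**Would it show?** Take var(log OR) = 3/[n r(1−r)(1−Σp³)], with n = 1,281, r the fee-for-service share and p the pooled category probabilities. The prior and the other model terms are ignored, and the fit is weighted by r, which moves the odds ratios slightly (1.29 at m = 20%). With 250 fee-for-service patients and m = 20%, the standard error is 0.130, log(1.289) = 0.254, and 0.254/0.130 = 1.96, so the posterior probability of a payer effect is about 0.975. Over 100 to 400 fee-for-service patients (stays missed only), it is 0.63 to 0.71 at m = 5%, 0.91 to 0.99 at 20%, and at least 0.98 at 30%.

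**Arm effect within fee-for-service.** Apply the same misses to both arms under a true arm odds ratio of 1.50. The observed value is 1.49, 1.48, 1.46 or 1.44 at 5%, 10%, 20% or 30% of stays missed, and 1.48, 1.46, 1.42 or 1.39 with deaths missed too. If detection differs by arm and there is no true effect, 30% missed under STS against 10% under RPM gives an arm odds ratio of 0.77.

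**The case against.** The strongest reply is that these are sensitivity analyses with no threshold or decision attached. The protocol says that the primary model stays as it is whatever the payer result, and that randomization protects the arm comparisons. Section 8.9.8 already re-estimates arm effects where ascertainment is best. The miss rates are the reviewer's, and at 5% little happens. All of this stands, and it limits the point to how the payer shift is interpreted.

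Four stronger readings are tempting, and the documents do not support them.

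- *The artefact imitates a payer interaction.* With equal misses by arm, the largest shift is log(1.50/1.387) = 0.078. The same variance formula gives the pooled RPM-versus-STS interaction a standard error of 0.42, 0.28 or 0.24 with 100, 250 or 400 fee-for-service patients, so the shift is at most about 0.3 standard errors. Detection that differs by arm would matter more. It is conceivable, because call-center staff review the charts of RPM non-responders, but the documents do not show that this affects the endpoint.
- *Payer and source are completely aliased.* Members who drop coverage also get records review, and the protocol's table of measures lists four sources without a payer split. The true gap may be smaller than Section 8.11.1 implies.
- *The analyses were written to justify adding fee-for-service patients.* Neither document says so. The protocol gives oversight as the reason for the DSMB reports.
- *Every fee-for-service survivor scores 90*, from the Section 6.1 definition of home. Section 8.11.1 gives these patients records review, so this is a wording gap to close and not how the endpoint would be scored.

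**Conclusion.** The concern holds for the payer-term and payer-specific-intercept models and for the DSMB payer reports. Each sets mainly claims-based home days beside records-review home days under a rule that turns unseen events into home days. With no true payer difference, the apparent odds ratio runs from 1.06 to 1.46 if stays are missed, and from 1.10 to 1.81 if deaths are missed too. These figures assume miss rates of 5% to 30%, complete loss of facility days in each missed survivor, complete detection in claims, and the baseline distribution of Table 2. Partial misses would give smaller values.

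The interaction and separate-fit models are only slightly attenuated unless detection differs by arm. A reader might infer that the primary result is compromised; unequal ascertainment by payer does not by itself favor an arm under randomization. The change is worth making because it is cheap and makes a planned analysis interpretable.

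**What to change.** 1. In Section 8.9.7, derive a second home-days value for Health Plan members from the non-claims data (EHR, HIE, participant report), using the sources and rules applied to fee-for-service patients. The protocol lists these sources in its table of measures, and its Data Collection section says "health care utilization data is extracted from electronic health records and payer claims at baseline and 90-days".
2. Fit the payer-term and payer-intercept models on this common-source value in patients randomized on or after August 10, 2022, keeping the severity and SNF terms.
3. Report agreement between claims-based and record-based home days in covered Health Plan members, by arm. This estimates what records review misses and shows whether detection differs by arm.
4. Where non-claims data are not available for members, report the payer odds ratio over a stated range of miss rates and label it payer plus data source. Use the same label in the DSMB payer reports.
5. Reconcile Section 6.1, Section 8.11.1 and the protocol's table of measures on the sources, and on what counts as home for a fee-for-service patient.

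The cost is extra programming and a less complete home-days value for members in this sensitivity analysis only. It should not depend on new manual chart review: Section 8.11.1 describes such review only for a small subset, and some recruiting hospitals are outside UPMC. A common source will not remove real payer differences, such as the protocol's exclusion of fee-for-service patients discharged to a SNF. The primary analysis is unchanged.

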#### 8.9.8. Sensitivity analysis limited to UPMC Health Plan members with coverage for the duration of follow up

We will conduct an analysis limited to patients with UPMC Health Plan coverage throughout the duration of the 90-day follow up period. FFS patients, as well as UPMC Health Plan members who lose or drop their coverage under the Plan before the end of the 90-day follow up period, will be excluded from this analysis. Outcomes ascertainment could be more accurate among patients included in this analysis. This analysis will be conducted using the model in 8.3.3.

### 8.10. Analyses of heterogeneity of treatment effect

#### 8.10.1. Comparison group determination for heterogeneity of effect analysis

Because it is possible for our RAR design to reduce enrollment to under-performing arms, we may be at a power disadvantage for identifying heterogeneity of treatment effect (HTE) of each active intervention compared with STS as a function of baseline covariates: age, sex, race, chronic comorbidity index, comfort with technology, health literacy level, Area Deprivation Index, discharge location, illness severity and admitting diagnosis. Therefore, we may pool arms prior to HTE analysis based on arms' average effects. For instance, if both RPM-Low and RPM-High are on average effective, we will pool these patients. However, we may choose not to pool patients by care team component (Standard Team or Enhanced Team) since resource utilization for these components is different and stakeholders have expressed a strong interest in identifying subgroups that benefit, especially among those who receive the Enhanced Team component. Thus, all analyses described below will be repeated for comparisons between each active (and potentially pooled) intervention and STS arms.

#### 8.10.2. Analysis of effect heterogeneity across pre-determined subgroups

We will conduct differential treatment effects analyses, comparing differences between RPM groups and STS across pre-specified subgroups of patient-level clinical, social, and environmental factors that could be potentially used to tailor service delivery. All analyses will be performed using a cumulative logit model for the primary PDHD outcome, including terms for treatment arm, subgroup, treatment by subgroup interactions, stratification variables, and calendar time of randomization. Subgroup variables and definitions were determined as plausibly related to treatment effect heterogeneity. Each subgroup variable will be analyzed in two ways: 1) four RPM arms kept separate; and 2) comparing standard team and enhanced team arms. Analyses will not be adjusted for multiple comparisons. Evidence of differential treatment effects across subgroup levels will be summarized using the posterior probability that interaction

terms are greater than 0. In addition, treatment effects by subgroup level will be summarized using the posterior median cumulative odds ratios from each model, and corresponding 95% credible intervals.

Subgroup definitions are as follows:

- Patient Age
  - <65 vs age ≥65
- Sex
  - Female vs male
- Race
  - White patients vs Black patients
- Chronic Condition index
  - CCI<5 vs CCI≥5
- Level of comfort with technology
  - Comfortable vs uncomfortable vs missing
- Health literacy level
  - Limited vs marginal vs adequate vs missing
- State-ranked Area Deprivation Index
  - Quartile 1 vs quartile 2 vs quartile 3 vs quartile 4 vs missing
- Location after discharge
  - Skilled Nursing Facility vs home
- Severity of illness
  - Severe (mechanical ventilation or vasopressor use during index hospitalization) vs not severe
- Discharge diagnosis
  - COVID vs Non-COVID Sepsis vs Other lower respiratory tract infection

### 8.10.3. Analysis of effect heterogeneity on dichotomized outcomes

We will explore potential heterogeneity of the effects of active arms compared to control groups after dichotomizing the PDHD outcome, collapsing all values of PDHD less than 90 into a single category. This will facilitate the estimation of conditional average treatment effects on the risk difference scale.

For our first set of analyses, we will dichotomize continuous or ordinal covariates, and analyze the conditional absolute risk differences (cARD) between the levels of the dichotomized covariates. For each covariate, we will test the null hypothesis that there is no difference in the cARDs using the Q test. We will also calculate 95% CI for the cARDs and their differences.

For our second set of analyses, we will use an “effect-based” approach to estimate ARDs conditional on multiple covariates simultaneously. In this approach, we will divide the data into two halves in approximately equal proportion. The first half will be used for cARD model derivation, as well as any missing data imputation models. We will compare the performance of several competing cARD models with different advantages and disadvantages, including causal forest, local linear random forest R-learners, and regularized logistic regression. We will compare these models in the derivation set using the following cross-validated performance metrics: area under the target operating characteristic curve (AUROC) and R-loss. The model with the best performance will be validated in the patients that were not used for model derivation. Model validation will be performed by examining the calibration of the model, including the estimation of calibration intercept, slope, and their 95% CIs. The presence of HTE identified by the model will be determined if the calibration slope p-value is <0.05. In addition, we will estimate ARDs and 95% CIs within quantiles of predicted cARDs generated from the derived model for each patient in the validation set. We will test the null hypothesis that the quantile ARDs are not monotonically increasing across the quantiles. Finally, to examine whether the results are dependent on the particular random derivation/validation split that was used, we will repeat the analyses across many different random splits and aggregate the results, including inferences, with the result from the original random split. If we are able to identify HTE using our selected best-performing cARD prediction model, we will determine the value of the predicted cARD that serves as the best classification rule for identifying the subgroup that benefits from each candidate intervention. Finally, we will explore which baseline characteristics predict treatment effectiveness by plotting the associations between baseline characteristics against cARD predictions, and a fit-the-fit approach using binary decision trees where the predicted cARD is treated as the outcome variable.

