## 12. Appendix

### 12.1. *Sepsis data for simulations*

To create realistic clinical trial simulations, we obtained pre-trial member-level data from UPMC for patients that were hospitalized from either sepsis, pneumonia, and/or a lower respiratory infection. Patients in this sample were at least 21 years old and deemed low risk for readmission (based on an internal UPMC risk score). We received 4718 records from members that received their insurance through Medicare or commercial plans. This data included the following covariates: age group, CCI, sepsis status, pneumonia status, LRTI status, whether a patient had mechanical ventilation, vasopressors, or was in the ICU. In addition, we have whether a patient was discharged to a SNF or to home, as well as their home days endpoint score. We additionally received 2737 records from members whose insurance is through Medicaid or SNP (special needs population). This data only contained the home days endpoint with no additional covariate information.

Using the totality of this data, we summarize the home days distribution by finding the proportion in each level of the outcome, as shown in the “Overall” column in Figure 2.

In addition, we summarize the two strata variables using the partial data with covariate information. We define the severe strata as patients who were on mechanical ventilation or vasopressors during their hospital stay. In this data, 11% of the population meets this definition. We define the SNF population as patients whose discharge status was “Discharge to SNF”, where 37% of the population meet this definition. Using these covariates, we estimate the relationship between the home days endpoint and the covariates, illness severity and discharge to SNF, using a frequentist ordinal regression. We estimate an odds ratio for severe illness compared to non-severe of 0.75 and an odds ratio for patients discharged to SNF compared to those discharged home to be 0.35. Under these estimated odds ratios, we transform the home days distribution (using the full data) for the severe strata and the discharged to SNF strata. The resulting distributions are presented in Figure 2. Patients who are not categorized as severe or were discharged straight to home are assumed to have the baseline home days distribution shown in the overall column.

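### Section 8.10.3 builds its benefit rule only on PDHD = 90 versus < 90, scoring death like one night in hospital, so it can rank higher-risk patients last although they gain more home days and lives.

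*Combined protocol and SAP*

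**What the plan says.** The primary endpoint (SAP 6.1) is ordinal, with death at the bottom: "Patients will be assigned -1 days if they die before day 90 post-discharge home". Short stays also cost days: "Any calendar day partially spent in acute care hospitals or post-acute care facilities is counted as a full day". So a patient who dies and a patient with one night back in hospital both fall below 90.

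For the heterogeneity work in 8.10.3 the outcome is redefined "after dichotomizing the PDHD outcome, collapsing all values of PDHD less than 90 into a single category". The one reason given in the text is the effect scale: "This will facilitate the estimation of conditional average treatment effects on the risk difference scale". Two sets of analyses use this indicator: one-covariate comparisons of conditional absolute risk differences (cARDs), and multivariable cARD models (causal forest, local linear forest, regularized logistic regression) with split-sample validation. If heterogeneity is found, the plan will determine "the value of the predicted cARD that serves as the best classification rule for identifying the subgroup that benefits". The covariates listed in 8.10.1 end with "discharge location, illness severity and admitting diagnosis", so the models see both risk strata.

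Section 8.10.2 analyses heterogeneity on the full ordinal PDHD, one pre-specified subgroup variable at a time, reported as cumulative odds ratios. No cARD model in 8.10.3 is fitted to home days or to death.

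**The concern.** Aim 2 is meant to show for whom each care model works best, and the protocol's Significance section ties it to directing the most resource-intensive interventions to those patients. The rule in 8.10.3 is the only planned product that combines several covariates into a statement of who benefits on an absolute scale.

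The indicator records one transition: from any PDHD below 90 to exactly 90. Moving a patient from death to 70 home days counts as nothing; removing a single inpatient night counts in full. In high-risk strata few patients are near 90 and many die, so the indicator has little room to move exactly where survival has most. A rule built on it may tell readers that the sicker patients are the lesser beneficiaries when, on the trial's own primary scale, they gain more.

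**Working it through.** **Inputs.** Table 2 baseline distribution (death, 0-19, 20-39, 40-49, 50-59, 60-69, 70-79, 80-89, 90): 0.133, 0.005, 0.017, 0.017, 0.026, 0.042, 0.077, 0.228, 0.454. It sums to 0.999 and is rescaled to 1. Stratum ORs (12.1, 12.2): severe 0.75, SNF 0.35, both 0.2625. Treatment OR constant across strata, as 8.3.2 assumes. My assumptions for mean days: bin midpoints and death = 0. Scoring death as -1, or using lower bin limits, does not change the order at ORs of 1.25 to 1.75.

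**Formula.** For every cut-point, odds(Y > j) are multiplied by the stratum OR and then by the treatment OR.

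**Reproducing the plan.** P(90), OR 1 to 1.5:
- Baseline: odds 0.4545/0.5455 = 0.833; × 1.5 = 1.250; P = 0.555. Gain 10.1 points.
- SNF: 0.833 × 0.35 = 0.2916, P = 0.226; × 1.5 = 0.4374, P = 0.304. Gain 7.9 points.

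Mortality:
- Baseline: odds 0.1331/0.8669 = 0.1536; ÷ 1.5 = 0.1024; P = 0.093. Fall 4.0 points.
- SNF: 0.1536/0.35 = 0.4388, P = 0.305; ÷ 1.5 = 0.2925, P = 0.226. Fall 7.9 points.

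Table 4 prints P(90) 0.45 to 0.55 and 0.23 to 0.30, and mortality 0.13 to 0.09 and 0.31 to 0.23. All probabilities in Tables 4 and 6 reproduce within 0.01. The conflict is visible in Table 4 itself: baseline gains 10 points of P(90) and 4 of survival; SNF gains 7 and 8.

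**Content of the collapsed class.** Baseline: 0.133/0.545 = 24% deaths and 0.228/0.545 = 42% with 80-89 days. SNF: 0.305/0.774 = 39% deaths; 80-89 days 26%.

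**Common OR, all four strata.**

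| OR | Gain | Baseline | Severe | SNF | Both |
|---|---|---|---|---|---|
| 1.25 | P(90), points | 5.6 | 5.4 | 4.1 | 3.5 |
| 1.25 | Home days | 2.9 | 3.4 | 4.4 | 4.7 |
| 1.5 | P(90), points | 10.1 | 9.9 | 7.9 | 6.8 |
| 1.5 | Deaths averted per 100 | 4.0 | 5.0 | 7.9 | 8.9 |
| 1.5 | Home days | 5.0 | 5.9 | 7.9 | 8.4 |
| 1.75 | P(90), points | 13.9 | 13.8 | 11.2 | 9.7 |
| 1.75 | Home days | 6.6 | 7.8 | 10.6 | 11.4 |

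The reason is simple. For a modest OR, a risk difference is roughly log(OR) × p(1 - p). Across the strata, p(1 - p) for PDHD = 90 falls (0.248, 0.237, 0.175, 0.147), while for death it rises (0.115, 0.141, 0.212, 0.233).

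**Where the reversal stops.**
- Larger ORs: at 2.25 the P(90) gains are 19.8 (baseline) and 20.0 (severe) points, so severe is no longer below baseline; the same holds at 3.06.
- Different ORs by stratum: with home discharges at 1.5, SNF patients gain more days but less P(90) only if their OR lies between about 1.29 and 1.66.
- ORs varying between patients around 1.5 (SD of log OR assumed): the rank correlation of P(90) gain with days gained is -1.00 at SD 0, +0.30 at 0.1, +0.74 at 0.2 and +0.87 at 0.3. With lives gained it is -1.00, +0.16, +0.62 and +0.79.
- No mortality effect (12.6), OR 1.5: P(90) gains 8.6 / 8.4 / 6.6 / 5.6 points; days 1.8 / 2.0 / 2.2 / 2.2. The spread in days is under half a day, and the last two strata are tied.

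**The case against.** The strongest reply is that a common OR means no heterogeneity on the plan's own modelling scale, while 8.10.3 exists to find patients whose effects differ. This stands as a limit. A reader might infer from the table that the rule will rank patients in the opposite order to their true benefit. The documents do not support that as a general statement: once ORs vary even modestly, the correlation turns positive, and the rule uses many covariates, not just these two strata.

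Second, the deaths averted, and most of the days gained, come from carrying the OR through to mortality. The protocol's primary-outcome paragraph expects only a small effect on time to death, and 12.6 simulates none. This also stands: in that setting the conflict is negligible in days and there are no lives to rank.

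Third, a reader might conclude that mean home days should replace the indicator. That is a trade-off. With no mortality effect at OR 1.5, the standardized effect on days is about 0.06 (1.8/31 at baseline; 2.2/39 in severe plus SNF). For P(90) it is about 0.15 to 0.17 (0.056/0.384 to 0.086/0.498), using untreated SDs. Derivation uses half the data, and 8.10.1 already warns of limited power.

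Fourth, 8.10.2 keeps the full ordinal scale for these same strata, 8.9.3 separates mortality from survivors' days, and 8.10.3 is described as exploratory. These soften the point but do not remove it. Under a common OR, 8.10.2 would rightly show no interaction and so say nothing about absolute gain; 8.9.3 concerns average effects; neither yields a multivariable rule.

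One can also construct a case in which SNF deaths are halved and every saved patient stays below 90 days, which gives a cARD of zero. It illustrates the blind spot, but no scenario in the plan produces it.

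**Conclusion.** The point holds in a conditional form. Every analysis in 8.10.3, including the benefit rule, treats death and a one-night readmission as equal. The rule can therefore place higher-risk patients below lower-risk ones although they gain more home days and lives. At the plan's ORs of 1.25 to 1.75, held constant across strata, the order over the four strata is fully reversed.

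This rests on the Table 2 distribution, the stratum ORs in 12.1 and 12.2, a proportional effect that reaches mortality, and, for days only, the bin midpoints. It does not show that the rule will mislead in the actual data. No success criterion or randomization rule depends on 8.10.3; what is at stake is the Aim 2 message about who benefits.

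**What to change.** In 8.10.3, keep the PDHD = 90 indicator. Add the same covariate tests, learners, split-sample validation and classification rule for two further outcomes: PDHD on its full scale (difference in mean home days, or in a mid-rank score that keeps death lowest) and 90-day mortality. Cross-tabulate the patients that each rule selects. State in advance that, where the rules disagree, no subgroup will be described as benefiting or not benefiting on the strength of the PDHD = 90 rule alone. The stated wish for an absolute scale is still met, because a difference in mean home days is also absolute and forest and R-learner methods accept a numeric outcome.

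The cost is SAP wording, extra model runs on data already collected, and more results to reconcile. Mean home days will be less sensitive than P(90) if the interventions leave mortality unchanged, which is why the indicator should stay.
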